### Budget Impact Analysis

The budget impact analysis (BIA) will be conducted as outlined in Mauskopf [21] to assess how health care budgets are changed when offering adjuvant CBTsa over a range of implementation levels. The BIA will be conducted from various perspectives: (1) wider societal perspective, i.e. including productivity losses; (2) the more narrow perspective of the public purse (in Dutch: Budgettaire Kader Zorg); down to (3) the narrow perspective of the health care insurer. In each perspective the following scenarios will be calculated a) a scenario in which the intervention is offered to 60% and 80% of the target group, and b) an extreme scenario in which 100% of the target group will be receiving the intervention. All scenarios will be compared with a base-case scenario, reflecting current care, where 0% of the target group is offered CBTsa.

### Cost analysis

When taking the societal perspective, we shall consider the costs of offering the health care interventions (also the interventions offered in routine medical care for this particular target group), patients' out of pocket costs, and costs stemming from productivity losses. Treatment costs will be based on the full economic cost prices (standard cost prices as reported in the Dutch Costing Manual); productivity losses will be valued using the average gender and age specific productivity levels in the Dutch working population. When taking the perspectives of the public purse (BKZ) and the health insurance companies' perspective, then the focus will be restricted solely to the direct medical costs and for these costs use will be made of the average tariffs of the Dutch Health Authority (NZA).

### Modelling approach

Use will be made of a health economic (Markov cohort) simulation model to be based on modelling techniques outlined in Briggs et al. [22]. The model will compare two health care systems: a base-case scenario representing usual care for patients and an alternative scenario representing usual care augmented by adjuvant CBTsa. Costs and effects will be modelled out over the short term (12 months) and longer-term (36 months). Long-term costs and effects will be discounted according to the Dutch guidelines. The model will be designed to conduct extensive sensitivity analyses over all cost, effect and discounting parameters simultaneously (cf. [22]). It is worth noting that the model will be populated using the excellent data available at AMC about the disease stages as occurring in the natural course of schizophrenia in a population at ultra-high risk of imminent psychosis, with further data on average PANSS scores per health state and the transition rates between those health states (cf. [23]). Therefore, we expect to be able to make a health economic model that will offer value beyond this study alone.

PATIENT OUTCOME ANALYSIS (INCREMENTAL NET-BENEFIT REGRESSION ANALYSIS)

The intervention might be effective and cost-effective in some population segments, but not in others. For example, smaller treatment benefits might be expected in patients presenting with higher levels of paranoia, comorbid disorders (especially axis-2 disorders) and in ethnic minorities. Effect modification analysis is often used to shed light on heterogeneity in treatment response owing to target group diversity. In the context of health-economic evaluations, the same kind of information is obtained using incremental net-benefit regression analysis (INBRA).

## Patient outcome analysis (INBRA)

INBRA relies on the same data as CEA, but now we prefer to have a clinical outcome on a continuous measurement scale [24]. For this we will make use of the PANSS. INBRA is essentially a regression analysis where the treatment dummy, a prognostically relevant population characteristic (e.g. Dutch vs non-Dutch ethnicity) and their interaction are regressed on net-benefits. Net-benefits, NB, are defined as,  $NB = (E * \pi) - C$ , where E are effects (changes on the PANSS),  $\pi$  is an unknown quantity representing the willingness to pay (WTP) for one unit of health gain (decrease on the PANSS-negative) and C are the additional costs of offering the adjuvant CBTsa intervention. Because  $\pi$  is an unknown quantity, we will use a range of plausible WTP levels in our analysis. Within the regression framework, INBRA essentially evaluates the net-benefits as a function of the effect modification and thus helps to answer the question: who benefits most? – or more precisely, are there any subgroups in which the intervention is particularly cost-effective. This information may aid future improvements of the CBTsa intervention such that it may become more cost-effective in subgroups that now do not fully benefit from the intervention or else these data may guide decisions about referring those patients to the intervention such that these people may derive full benefit from the intervention in a cost-effective way.

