#### Anticipated Cost-Effectiveness/ Budget Impact

A secondary aim of the present study is to examine the cost-effectiveness of this new type of intervention. We based our estimated cost-effectiveness on the following calculation:

1. Costs of the intervention per patient are estimated at 800 Euro.
2. We expect a reduction in negative symptoms with an effect size of .66 compared to standard care only [3].
3. There is a small effect or no effect of usual care on negative symptoms [3&5]. Since the exact effect is unclear and our concern is the additional effect, we set the effect of usual care at 0, and use the effect of our intervention (effect size 0,66) compared to usual care. Assuming that negative symptoms resemble depression, and that negative symptoms persist half a year, this amounts to a QALY gain of  $0,66 \text{ (effect size)} \times 0,172 \text{ (conversion factor d->dw)} \times 0,5 \text{ (duration of half a year)} \text{ per patient} = 0.057$ .
4. The costs for an additional QALY then are  $800/0,057 = \text{€}14.035,09$  per additional QALY.
5. This is below the €20.000 cut-off, as a result of which the intervention may be considered costeffective

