#### Cost Effectiveness Analysis (CEA):

The economic evaluation will be conducted as a cost-effectiveness analysis, CEA, with costs / treatment responder, and a cost-utility analysis, CUA, using quality adjusted life years (EQ-

5D/QALYs) as a generic measure of health gains. Both the CEA and the CUA will be conducted from the societal perspective and in agreement with the intention to treat principle. The trial's follow-up measurements do not exceed the time horizon of one year and therefore neither costs nor effects will be discounted. Sensitivity analyses will be directed at uncertainty in the main cost-drivers.

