### Cost analysis

We will consider four types of costs: (1) the costs of offering the intervention, (2) costs stemming from health care uptake including the costs of medication, (3) patients' out-of-pocket costs, (4) costs stemming from productivity losses due to absenteeism and lesser efficiency while at work and owing to changes in the contractual number of work hours per week. The first two types of costs are also known as the direct medical costs and these will be based on the full economic costs of offering the interventions. For this we shall make use of the pertinent Dutch guideline for economic evaluation [18], and rely on the standard cost prices reported therein. The patients' out-of-pocket costs are known as direct non-medical costs and encompass the patients' costs of travelling to health services and parking costs incurred in the context of health care uptake. Finally, productivity losses will be based on the gender and age specific friction costs, as outlined in the Dutch guideline for costing. Data on resource use (health care uptake) and productivity losses will be collected with the latest version of the Trimbos/iMTA Questionnaire Costs associated with Psychiatric illness, TiC-P, [19]. The TiC-P is the most widely used health service receipt interview for economic evaluations in the Netherlands.

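### The net-benefit regression counts only the cost of offering CBTsa, so it leaves out three of the four cost types in the protocol's own societal analysis

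*Protocol*

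**What the plan says.** All references are to the Protocol.

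- **Patient outcome analysis (INBRA)** gives NB = (E × π) − C. On cost, "C are the additional costs of offering the adjuvant CBTsa intervention". On effect, "where E are effects (changes on the PANSS", with no direction attached. The willingness to pay π is the price "for one unit of health gain (decrease on the PANSS-negative". Net benefit is regressed on treatment, a patient characteristic and their interaction. The aim is to find subgroups in which CBTsa is especially cost-effective, possibly to guide referral.
- The same section opens with "INBRA relies on the same data as CEA".
- **Cost Effectiveness Analysis (CEA)**: "Both the CEA and the CUA will be conducted from the societal perspective".
- **Cost analysis** (under the CEA, section 5.4): "We will consider four types of costs: (1) the costs of offering the intervention, (2) costs stemming from health care uptake". The list goes on to patients' out-of-pocket costs and productivity losses. Resource use and productivity are collected with the TiC-P.
- **Anticipated Cost-Effectiveness/ Budget Impact**: "Costs of the intervention per patient are estimated at 800 Euro".

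**The concern.** Net-benefit regression needs each patient's own total cost, in both arms, from the perspective chosen for the evaluation. The definition of C names only the cost of providing the therapy, in nearly the words used for type (1) of the four. Two statements in the INBRA section therefore cannot both be followed literally: the definition of C, and the reliance on CEA data, which are societal and cover four cost types.

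At stake is what the subgroup analysis can find. The hypotheses in section 1 expect CBTsa to lower need for care, and productivity losses are a named secondary outcome. Subgroups may differ through such savings as well as through symptom change. If C excludes them, the analysis becomes close to ordinary effect modification on the PANSS, rescaled by π. A question about cost-effectiveness would then be answered with almost no cost information.

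**Working it through.** **1. The plan's own figure.** The only stated result that uses the offering cost is the anticipated cost per QALY: 0.66 × 0.172 × 0.5 = 0.05676, rounded to 0.057, and 800 / 0.057 = EUR 14,035.09. It reproduces (unrounded: 800 / 0.05676 = EUR 14,094). It is not in dispute, and is used here only as the source of EUR 800.

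**2. What the interaction term contains.** Net benefit is linear in E and C, so the treatment-by-subgroup coefficient splits exactly:

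δ(NB) = π × δ(E) − δ(C), with δ(C) = δ(C1) + δ(C2) + δ(C3) + δ(C4)

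C1 to C4 are the costs of the intervention, health-care use, out-of-pocket items and productivity losses. As written, δ(C) = δ(C1). The other three terms are absent whatever their size.

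**3. How much C1 can vary.** It need not be constant among CBTsa patients: section 3.1 allows individual sessions over 6 to 8 weeks and adapts session time to the patient. As a rough bound, assume full attendance at weekly sessions of equal length, with the whole EUR 800 due to the individual sessions. If EUR 800 is the cost of 8 sessions, 6 cost 800 × 6/8 = 600, a difference of 200. If it is the cost of 6, then 8 cost 800 × 8/6 ≈ 1,067, a difference of 267. Missed or reshaped sessions could widen this. C1 can therefore contribute something, but it carries no information on savings elsewhere.

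**4. Effect on the treatment contrast.** Inputs: offering cost EUR 800 (Protocol); a 5-point PANSS-negative improvement counted as +5, π = EUR 200, and a difference D in all other costs (all assumed). As written, the result is 5 × 200 − 800 = +200 for every D. With full costs it is 5 × 200 − (800 + D):

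| D (EUR) | C as written | All four types |
|---|---|---|
| −3,000 | +200 | +3,200 |
| −1,000 | +200 | +1,200 |
| 0 | +200 | +200 |
| +1,000 | +200 | −800 |
| +3,000 | +200 | −2,800 |

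The protocol gives no π. Over π = 100, 200, 500 and 1,000 the as-written value 5π − 800 is −300, +200, +1,700 and +4,200. The conclusion changes sign once D passes that same value.

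**5. Effect on the interaction.** A simulated regression (200,000 patients, π = 200, offering cost 800) gave both subgroups the same PANSS effect and placed a EUR 2,000 saving in other costs in one subgroup only. By step 2 the expected coefficients are 0 with C as written and 0 − (−2,000) = 2,000 with full costs. The fitted values were about 9 and about 2,045, the departures being simulation noise. With C as written, the saving is not seen.

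**The case against.** **The cost wording may be looser than it looks.** The INBRA section relies on CEA data and announces only one departure, a continuous outcome. It announces no change of perspective. The protocol also uses the language of offering care more broadly elsewhere: Cost analysis applies it to the first two cost types together, and the cost section of the budget impact analysis extends it to routine care. C could therefore be meant as the full incremental cost of adding CBTsa. That reading is possible, and it shows that the intent may be right. It does not override an explicit definition that matches type (1) almost word for word, and an analyst working from the formula would omit the rest.

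**A reader might infer that C is fixed within each arm and so adds nothing to the interaction.** The documents do not support that. EUR 800 is a planning estimate, and session number and length may vary.

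**A reader might infer a sign error, with improvement counted as negative benefit and the subgroup ranking reversed.** If E were coded as follow-up minus baseline, a 5-point improvement at π = 200 would give −5 × 200 − 800 = −1,800 instead of +200. Nothing in the section prescribes that coding. The same sentence prices a decrease on PANSS-negative as the unit of health gain, and E counted in that unit has the correct sign. What stands is that E has no stated direction and that the scale moves from PANSS to PANSS-negative within one sentence. The word increase in the response definition under CEA and CUA is a separate matter.

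**INBRA is a subgroup exploration within a secondary objective.** This is true and limits the weight of the point. The clinical analysis, the ICERs and the budget impact analysis do not use this C. The issue is nevertheless not a detail left to an analysis plan: the protocol states a definition, and that definition conflicts with its own perspective.

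**Conclusion.** The cost point holds. C as defined covers one of four cost types and conflicts with the societal perspective and with the reliance on CEA data. Followed literally, the treatment-by-subgroup term reflects the PANSS effect and any variation in delivery cost, and a subgroup that is cost-effective through savings cannot be identified. The structural result in step 2 needs no assumption. Its size in euros depends on π and on cost differences that the protocol does not give, so the figures 9 against 2,045, and +200 against a range of −2,800 to +3,200, are illustrations only.

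The direction of E is an ambiguity worth closing. The documents do not support a claim that the plan reverses the sign or the ranking. The correction should be made, but it concerns a secondary economic analysis and does not touch the primary result.

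**What to change.** In Patient outcome analysis (INBRA):

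1. Define C_i as patient i's total societal cost over the trial, summing all four types in Cost analysis, for patients in both arms. Delivery cost should be what the patient actually received.
2. Define E_i as baseline minus follow-up PANSS-negative, so that a decrease is positive and E is on the scale that π prices. Name the follow-up time.
3. Regress NB_i = π × E_i − C_i on treatment, the characteristic and their interaction, over the planned range of π.

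The cost is two definitions in the text. No new data collection is needed, because the TiC-P and the PANSS are already planned.

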**5.5 Other study parameters**

Substance abuse, and socio-demographic variables (e.g. age, gender, medication prescription) will be added to the model as possible confounders.

## 6. ETHICAL CONSIDERATIONS

### 6.1 Regulation statement

The study will be conducted according to the principles of the Declaration of Helsinki (October 2008) and in accordance with the Medical Research Involving Human Subjects Act (WMO).

### 6.2 Recruitment and consent

Patients hospitalized or attending day-treatment at the Department of Early Psychosis, Amsterdam, the psychosis department of the ABC team, Utrecht and Centrum First Psychosis, Parnassia, The Hague will be checked for eligibility and asked for consent. To maximise engagement, group therapy will be presented as part of the standard dayprogram.

If a psychiatrist or physician of any the above-mentioned institutes sees a patient who meets our inclusion criteria, s/he will introduce the study, and intervention briefly to the patient. The academic research assistant will then approach the patient. To this end, s/he will provide oral and written information about the study (see Informed Consent).

In order to enhance the awareness of the study among professionals employed by the above institutes, the principal investigators and researchers will give talks at these institutes and stick posters to walls. The patients will be given approximately 48 hours to consider their participation.

Baseline assessments will be conducted by a RA blind to study condition and shortly after randomisation (see flowchart). The group therapy will commence after 16 participants (8 ST and 8 RCT) signed written informed consent; at maximum one month after baseline assessment.

### 6.3 Benefits and risks assessment, group relatedness

Risks: In the literature covering Cognitive Behavioural Therapy no risks, side effects or adverse effects have been described.

Benefits: recent evidence shows that modifying dysfunctional beliefs may improve negative symptoms and thereby functional outcome and social participation. With this intervention early in the course of the disorder we hope a) to prevent social withdrawal and diminish negative symptoms, thereby preventing the young patient from dropping-out of his/her social roles and from early social exclusion and/ or b) to help regain social roles when drop-out already occurred.

#### **6.4 Compensation for injury**

Given that no relevant risks are attached to the participation in the study, the Medical Ethical Committee obtained a release from the obligation to conclude special indemnity insurance for participants.

#### **6.5 Incentives (if applicable)**

Travel expenses and a total amount of 40 euro for the assessment of the test battery at baseline- end -of-treatment and 6 month follow-up will be reimbursed. Patients will receive 10 euros for completion of the first assessment, 20 if they participate in both baseline and the end-of-treatment assessment and 40 if they complete all three measures.

**6.7 Amendments**

Amendments are changes made to the research after a favourable opinion by the accredited METC has been given. All amendments will be notified to the METC that gave a favourable opinion.

**6.8 Annual progress report**

The sponsor/investigator will submit a summary of the progress of the trial to the accredited METC once a year. Information will be provided on the date of inclusion of the first subject, numbers of subjects included and numbers of subjects that have completed the trial, serious adverse events/ serious adverse reactions, other problems, and amendments.

**6.9 End of study report**

The investigator will notify the accredited METC of the end of the study within a period of 8 weeks. The end of the study is defined as the last patient's last visit.

In case the study is ended prematurely, the investigator will notify the accredited METC within 15 days, including the reasons for the premature termination. Within one year after the end of the study, the investigator/sponsor will submit a final study report with the results of the study, including any publications/abstracts of the study, to the accredited METC.

**6.10 Public disclosure and publication policy**

The results of scientific research involving human subjects must be disclosed unreservedly and there are no objections on this regard.

